#### 1. Activity Log

##### 1.1. SAP revisions

6 November 2020: First version (V1)  
20 November 2020: Second version (V2)  
8 December 2020: Third version (V3)  
9 December 2020: Fourth version (V4)  
18 December 2020: Fifth version (V5)  
21 January 2021: Sixth version (V6)  
21 January 2021: Eight version (V8)  
5 March 2021: Ninth version (V9)  
30 July 2021: Tenth version (V10)  
16 August 2021: Eleventh version (V11)  
07 September 2021: Twelfth version (V12)  
28 September 2021: Thirteenth version (V13)

#### 2. Study Overview

##### 2.1. Background and introduction

Preterm birth is in quantity and severity the most important issue in obstetric care in the world. In Australia, preterm delivery occurs in approximately 8.6% of all deliveries, while these rates rise to 63% for multiple pregnancies. Preterm delivery can either be iatrogenic (i.e. medically indicated) or spontaneous, with iatrogenic preterm birth being 3.9% and spontaneous onset being 4.7% of all deliveries in 2013.

Spontaneous preterm birth is linked to adverse outcomes, including increased risk of infant mortality and severe morbidity, and is associated with an increased risk of spontaneous

preterm birth in a subsequent pregnancy. Prevention of spontaneous preterm delivery is therefore a major perinatal research priority.

A preventative strategy for spontaneous preterm birth is dependent on the identification of high-risk women and the effectiveness of subsequent treatment. Potential treatments include cerclage, pessary and progestogens, while aspirin (certain) and dietary interventions (likely) are also effective.

The focus of this project is on the identification of high-risk women for spontaneous preterm delivery. Over the last decades, many studies have been performed to address prediction of spontaneous preterm birth. However, coordination of these efforts has been lacking and therefore research resources have been used suboptimally. To allow optimal use of current data, the best type of evidence synthesis is individual participant data (IPD) meta-analysis.

Background, rationale and general methodology of the IPPIC-II project have been documented in the grant proposal.

Previous evidence suggests that mid-trimester transvaginal ultrasonographic cervical length (CL) measurement may be an important predictor of spontaneous preterm birth. This statistical analysis plan sets out the analyses for an IPD meta-analysis assessing the value of mid-trimester transvaginal ultrasonographic CL measurement in predicting preterm birth. The plan proposes a method of quantifying changes in the probability of preterm birth, accounting for mid-trimester cervical length among other potential effects.

These methods have been selected to best allow for the effects to be incorporated into future decision support tools.

## 2.2. Aims and hypotheses

This study aims to assess whether a transvaginal ultrasonographic cervical length measurement in the second trimester can predict spontaneous preterm birth in asymptomatic women with twin pregnancy, with or without additional risk factors. We will assess women with singleton pregnancy in a separate parallel study.

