### *IPD meta-analysis*

The primary outcome of interest for the analysis will be the association between CL measurement and the incidence of preterm birth. We will perform a two-stage IPD meta-analysis.

The first stage will comprise building regression models for each study, using all the explanatory variables available in each study. Correlations between multiples will be accounted for in the analyses. We will build cox proportional hazard models and present hazard ratios with 95% confidence intervals. We will build multiple models, as follows:

- 1) **Basic model including only cervical length as a predictor (Model 1) – primary model**
- 2) Model with only key demographic predictors (mother's age, nullipara) and cervical length (Model 2)
- 3) Model with all predictors in table 1 (Model 3)
- 4) Model with all predictors in table 1, only including studies that include all predictors (Model 4)

In the second stage, the results of the study-level regression models will be meta-analysed in a random-effects model. Forest plots will be presented for all models, and between-study heterogeneity will be determined using  $I^2$  statistic, between-study heterogeneity variance  $\tau^2$  and the prediction interval. Small study effect will be investigated with contour enhanced funnel plots.

We will present cumulative incidence curves to visualise Model 1.

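### The SAP states a prediction aim but plans only measures of association, so it can show that cervical length is prognostic but not how well it predicts

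*SAP*

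**What the plan says.** Section 2.2 gives the aim in twin pregnancy: "This study aims to assess whether a transvaginal ultrasonographic cervical length measurement in the second trimester can predict spontaneous preterm birth". Section 2.1 frames the project in the same terms. It describes an individual participant data meta-analysis "assessing the value of mid-trimester transvaginal ultrasonographic CL measurement in predicting preterm birth", and adds: "The plan proposes a method of quantifying changes in the probability of preterm birth, accounting for mid-trimester cervical length among other potential effects". It then names the intended use: "These methods have been selected to best allow for the effects to be incorporated into future decision support tools".

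Section 4.3 (IPD meta-analysis) sets a different target: "The primary outcome of interest for the analysis will be the association between CL measurement and the incidence of preterm birth". On the output it says: "We will build cox proportional hazard models and present hazard ratios with 95% confidence intervals". The models are:

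- Model 1 (primary): CL alone.
- Model 2: maternal age, nulliparity and CL.
- Model 3: all Table 1 predictors, using what each study has.
- Model 4: all Table 1 predictors, in studies that have all of them.

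CL is itself a row of Table 1, so Models 3 and 4 contain it too. Section 4.3 also plans cumulative incidence curves for Model 1, and I², τ² and a prediction interval for the pooled ratios. Section 4.5 adds logistic models reported as odds ratios, and a spline-type analysis of the shape of the CL relationship. Section 3 assesses risk of bias with QUIPS.

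**The concern.** Whether a marker is associated with an outcome and how well it predicts that outcome are different questions. A hazard ratio says how the rate changes with CL. It does not say how well CL separates women who will deliver early from those who will not, or whether predicted risks agree with observed ones. Those are the properties that matter for identifying high-risk women and for a decision tool.

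With several thousand women, a pooled hazard ratio can be estimated very precisely while discrimination stays modest. If the publication answers the stated aim from the hazard ratios alone, its conclusion about prediction would go further than the analysis behind it. Because no model omits CL, any gain in accuracy over age, parity, obstetric history and chorionicity also goes unmeasured.

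**Working it through.** The SAP gives no event count, power or performance figure on this point, so there is nothing of its own to reproduce. The check is an inventory of planned outputs, followed by an illustration of scale.

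**Inventory (sections 4.3 to 4.5)**

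| Planned output | Measures predictive performance? |
|---|---|
| Hazard ratios, Models 1–4 | No: association, adjusted in Models 2–4 |
| Odds ratios, binary sensitivity analyses | No: association |
| I², τ², prediction interval | No: spread of the pooled ratio across studies |
| Subgroup interaction terms | No: whether the association differs between groups |
| Cumulative incidence curves, Model 1 | Displays absolute risk; no CL groups or accuracy measure stated |
| Splines | No: shape of the association |

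Models containing CL: 4 of 4. Models without CL: 0 of 4. Discrimination, calibration or classification measures planned: 0.

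**Illustration**

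Inputs:
- N = 7,039, the sum of the 15 rows listed in Table 2: 193 + 459 + 318 + 1102 + 385 + 223 + 593 + 463 + 256 + 383 + 199 + 103 + 911 + 1229 + 222. The text above the table says 17 studies, so the true total may differ.
- Spontaneous preterm birth rate: not given in the SAP; assumed 20%, 30% and 40%.
- Hazard ratio per SD of shorter CL: assumed 1.5, with 2.0 and 3.0 for comparison.

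*Precision.* The 95% half-width on the log hazard ratio per SD is 1.96/√(events), ignoring between-study heterogeneity. For a hazard ratio of 1.5, ln 1.5 = 0.405 and z = 0.405 × √(events).

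| Assumed rate | Events | Half-width | z |
|---|---|---|---|
| 20% | 1,408 | 1.96/√1408 = 0.052 | 15 |
| 30% | 2,112 | 1.96/√2112 = 0.043 | 19 |
| 40% | 2,816 | 1.96/√2816 = 0.037 | 22 |

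Random-effects pooling would widen these intervals. For the interval around 1.5 to reach 1, the half-width would have to grow to 0.405. That is about 8 times the 20% figure (0.405/0.052) and 11 times the 40% figure (0.405/0.037).

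*Discrimination.* For a normally distributed predictor under proportional hazards without censoring, C = E[1/(1 + exp(−b|d|))], with b = ln(HR per SD) and d ~ N(0, variance 2).

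| HR per SD | C |
|---|---|
| 1.5 | 0.61 |
| 2.0 | 0.67 |
| 3.0 | 0.74 |

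*Cross-check on the binary scale* (equal-variance binormal model). AUC = Φ(ln OR/√2), and sensitivity at a 10% false-positive rate = 1 − Φ(1.282 − ln OR). An odds ratio of 1.5 per SD gives AUC Φ(0.287) = 0.61 and sensitivity 1 − Φ(0.876) = 19%. An odds ratio of 2 gives AUC 0.69 and sensitivity 28%.

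A hazard ratio 15 or more standard errors from the null, before heterogeneity, is thus compatible with a C-statistic of about 0.61.

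**The case against.** The strongest reply is that this is a prognostic-factor study with loose wording. Section 4.3 openly names association as its target, QUIPS suits that question, and section 2.1 speaks of effects to be used in future tools, not of a tool to be validated here. Nor does the SAP say that significance will be read as useful prediction; section 4.2 only sets α. This stands, and it is why restating the aim is an acceptable repair. It does not remove the mismatch, because sections 2.1 and 2.2 still promise an answer about prediction.

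A reader might infer four stronger things that the SAP does not support:

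- *That the plan yields nothing but ratios.* It also plans cumulative incidence curves and splines. They do not measure accuracy, but they are there.
- *That the question cannot be answered at all.* Model 1 tests whether CL is prognostic. Models 2–4 show whether that association persists after adjustment. What is missing is how well CL predicts.
- *That what CL adds to other predictors is part of the section 2.2 aim.* It is not. The nearest wording is in section 2.1, which speaks of value and of other effects.
- *That the plan will misread a change in the CL hazard ratio from Model 1 to Model 4.* The two can rest on different studies, so such a comparison would mix adjustment with selection. The SAP does not say it will interpret that change, and it declares Model 1 primary.

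**Conclusion.** The concern holds as a mismatch between aim and analysis. Followed exactly, the plan would deliver a valid estimate of prognostic association and a picture of absolute risk by CL. It would deliver no measure of discrimination or calibration and no estimate of the gain over other predictors. The primary hazard ratio is not invalid; the point is what may be concluded from it. The change should be made, but it is an improvement and not a fatal defect.

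The inventory rests on the SAP text alone. The scale (half-width 0.037–0.052 on the log hazard ratio, C about 0.61 at a hazard ratio of 1.5) rests on the assumed 20–40% event rate, the 15 listed rows, a normally distributed predictor, no censoring in the concordance formula and no heterogeneity. The hazard ratio of 1.5 is illustrative and is not a forecast of the result.

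**What to change.** Add to section 4.3:

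1. For Model 1, report the C-statistic in each study and pool it by random effects.
2. In the Model 4 studies, on the same complete-case women, fit the Model 4 predictors with and without CL. Keep the two models otherwise identical, including gestational age at measurement, so that only CL differs. Pool the change in C.
3. Optionally, report the calibration slope by leave-one-study-out validation. This needs its own specification, because two-stage pooling of hazard ratios does not by itself define a single multivariable model to validate.

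Base statements about how well CL predicts on these measures, and describe the hazard ratios as prognostic association. If the measures are not added, restate the aim in sections 2.1 and 2.2 as prognostic association and limit the conclusions to match.

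The cost is SAP wording and modest extra analysis of data already being collected. The headline may look less favourable than a significant hazard ratio. The comparison with and without CL is limited to studies holding every Table 1 predictor. That set may be small: history of preterm birth is in Table 1 but absent from the section 5 list of available variables.

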## 2.3. Presentation of results

The validity of the conclusions will be discussed with members of the participating studies. The results and insights from this analysis will be published in a peer-reviewed journal, and presented at relevant conferences.

## 2.4. Variables of interest

### 2.4.1. Outcomes

#### *Primary outcome*

The primary outcome is gestational age in weeks at spontaneous preterm birth (time-to-event outcome). This is calculated by censoring the outcome of gestational age at 37 weeks to only include spontaneous preterm births, and calculating survival models. Studies that also reported medically indicated preterm birth, are treated as censored observation.

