#### *Secondary outcomes*

We will consider the following secondary outcome:

- Time to any type of preterm birth (spontaneous or iatrogenic, any cause). This is calculated by censoring the outcome of gestational age at 37 weeks to only include any preterm birth, and calculating survival models.

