**Table1. Predictors of gestational age in the model analysis for multiple pregnancies**

| Variable name  | Description                          | Values                            |
|----------------|--------------------------------------|-----------------------------------|
| Age_mother     | Mother's age                         | numeric                           |
| Nullipara      | Nullipara                            | 0=no; 1=yes                       |
| Hx_PTB         | History of preterm births            | numeric                           |
| Chorionicity   | Chorionicity in multiple pregnancies | 1=monochorionic;
2=dichorionic |
| CL             | Cervical length                      | [mm]                              |
| GA_measurement | Gestational age at CL measurement    | [weeks]                           |

Predictor selection among pre-specified clinically meaningful predictors will be guided by:

- Availability of data across studies (only predictors that are available for at least 50% of data points will be included)
- Descriptive analyses of association between predictor and outcome

In cases where multiple CL measurements are available per participant, we will select the measurement closest to 20 weeks gestation due to its proximity to the usual morphology ultrasound.

In addition, only CL measurements taken between gestational week 16 to 24 will be included in the analysis. In cases where only a range for gestational age at the time of measurement of the cervical length is provided for the entire individual study rather than individual level data, the mean of that range will be imputed as the gestational age.

All predictors will be specified before we start building models in our main analysis.

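### No entry time is stated for survival models on the gestational-age scale, so cumulative incidence before 24 weeks comes out too low where scan weeks vary; the CL hazard ratio is barely affected

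*SAP*

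**What the plan says.** SAP 2.4.1 defines the time axis: "The primary outcome is gestational age in weeks at spontaneous preterm birth (time-to-event outcome"). It then fixes the right-hand end of follow-up: "This is calculated by censoring the outcome of gestational age at 37 weeks to only include spontaneous preterm births, and calculating survival models". The secondary outcome has the same construction: "This is calculated by censoring the outcome of gestational age at 37 weeks to only include any preterm birth, and calculating survival models".

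SAP 2.4.2 sets the condition for being in the data: "only CL measurements taken between gestational week 16 to 24 will be included in the analysis". Where a woman has several scans, "we will select the measurement closest to 20 weeks gestation due to its proximity to the usual morphology ultrasound". Where a study supplies only a range of scan weeks, "the mean of that range will be imputed as the gestational age".

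SAP 4.3 fits Cox models study by study, pools them by random effects, names the CL-only Model 1 as primary, and draws cumulative incidence curves from Model 1.

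The SAP names no time origin, no start of the risk period, no left truncation and no lower gestational limit for an event. The scan week ("Gestational age at CL measurement") appears in Table 1 as a covariate, so it can enter Models 3 and 4 but not Model 1.

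**The concern.** With gestational age as the time scale, a woman becomes observable only at her scan. A woman scanned at 23 weeks could not have been recorded as delivering at 19 weeks, because she would then have had no 23-week scan. Without an entry time she still sits in the denominator at 19 weeks. The numerator holds only deliveries among women already scanned, while the denominator also holds women not yet scanned. The early hazard is therefore too small.

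At stake is the early part of the absolute-risk curves. SAP 2.1 describes the aim as quantifying the probability of preterm birth for later decision support, so absolute risk is an intended product. The early curve would reflect each study's scan schedule as well as its birth pattern. Adjusting for scan week in Models 3 and 4 does not repair the risk sets.

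**Working it through.** **Inputs from the SAP.** Time axis is gestational age; censoring at 37 weeks; scans from 16 to 24 weeks, a span of up to 8 weeks; GA_measurement and GA_delivery both listed in Section 5; 7,039 women as the sum of the 15 rows of Table 2. The SAP gives no event count, early risk or scan distribution, so it has no figure to reproduce.

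**Assumptions not in the SAP.** The early risks, the scan distributions, the fall of CL with gestation and the true hazard ratios below are all assumed. The window is taken to close at 24.0 weeks.

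**Step 1: closed-form approximation.** Let h be a small constant weekly hazard and F(t) the share of included women already scanned by week t.

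- No entry time: estimated hazard ≈ h·F(t). Summed to week 24 this is h × (24 − mean scan week).
- Delayed entry: estimated hazard ≈ h from the earliest scan. Summed to week 24 this is h × (24 − earliest scan week).
- Ratio ≈ (24 − mean scan week) / (24 − earliest scan week).

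Results: scans even over 16–24 weeks, (24 − 20)/(24 − 16) = 4/8 = 0.50. Scans at 18–22 weeks peaking at 20, (24 − 20)/(24 − 18) = 4/6 = 0.67. Scans even over 20–24 weeks, (24 − 22)/(24 − 20) = 2/4 = 0.50. All scans in one week, ratio 1, so no distortion after that week.

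**Step 2: simulation of 24-week cumulative incidence.** 7,039 women, six runs per scenario, about 35% spontaneous preterm birth by 37 weeks, indicated births censored, true HR per mm 0.93 before and 0.95 after 24 weeks. No-entry figures are means over runs; delayed-entry figures are medians.

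| Scan weeks | Assumed risk, 16–24 wk | No entry | Delayed entry | Shortfall |
|---|---|---|---|---|
| even, 16–24 | 0.5% | 0.25% | 0.51% | 51% |
| | 2% | 0.92% | 1.81% | 49% |
| | 5% | 2.38% | 4.73% | 50% |
| peaked, 18–22 | 0.5% | 0.23% | 0.33% | 30% |
| | 2% | 0.94% | 1.38% | 32% |
| | 5% | 2.40% | 3.50% | 31% |
| even, 20–24 | 0.5% | 0.13% | 0.26% | 50% |
| | 2% | 0.49% | 0.85% | 42% |
| | 5% | 1.16% | 2.28% | 49% |

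Shortfall = 1 − (no entry / delayed entry), for example 1 − 0.94/1.38 = 32%. The pattern follows Step 1.

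A separate simulation (12 runs of 7,000 women, even scans over 16–24 weeks) gave 0.58%, 1.74% and 2.70% against true risks of 1.00%, 2.96% and 4.88%: 42%, 41% and 45% too low. A third, with assumed risks of 1% and 3% and the same scan spread, gave 0.61% against 1.21% and 1.46% against 2.68% without and with delayed entry.

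**Step 3: carry-over.** By 37 weeks the gap is about 0.1 to 1.6 percentage points. The smallest is 33.61% against 33.70% (peaked scans, 0.5%). The largest is 34.89% against 36.49% (even over 16–24 weeks, 5%).

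**Step 4: hazard ratio.** In the 7,000-woman simulation (CL falling 0.8 mm per week) the log-HR per mm without and with entry was −0.0573/−0.0576, −0.0562/−0.0571 and −0.0545/−0.0559, an attenuation of 0.5%, 1.6% and 2.5%. In the simulation of Step 2 the change in HR per 10 mm was 0.005 or less in all but one scenario. The exception (5% early risk, even scans over 16–24 weeks, CL falling 1 mm per week) gave 0.634 against 0.623; on the log scale −0.456 against −0.473, about 3.7%. Restricted to women delivering or censored at 24 weeks or later, the two fits are identical (−0.0456 per mm in both).

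**The case against.** The strongest reply is that the main result is safe. The SAP reports hazard ratios with Model 1 as primary, these hardly move, and no estimate before 24 weeks is planned as such. The binary sensitivity analyses in SAP 4.5 do not use a survival time scale. This stands, and it limits the point to the curves and the early baseline hazard.

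Second, Cox models are fitted within studies, so differences in scan week between studies cannot distort a risk set; only spread within a study can. This also stands. The simulations pooled all women under one scan distribution and gave even scans over 16–24 weeks the widest spread the plan allows. Choosing the scan nearest 20 weeks argues for a narrower spread, closer to the 30% figure or below it. A reader might infer that every cumulative incidence curve is biased. The SAP does not support that: a study that scans everyone in nearly the same week shows almost no distortion.

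Third, the no-entry figure is the true proportion of scanned women who deliver before 24 weeks. That is correct as a description. But it mixes women who became observable at different weeks, so it is not a risk from any stated starting point and does not carry over to a setting with another scan schedule.

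Fourth, a reader might infer that the SAP rejects delayed entry. It does not; it is silent on the start of risk. Because the end of follow-up is stated and the start is not, a survival call without an entry argument is the literal reading.

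**Conclusion.** The point holds as a gap in specification with a predictable direction. Followed as written, the plan understates cumulative incidence before 24 weeks in studies with spread-out scan weeks. The shortfall at 24 weeks is roughly 30–50% relative, for assumed early risks of 1–5% and the scan spreads examined. In absolute terms this is at most a few percentage points, and well under one if early births are rare.

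The direction follows from the design alone. The size rests on early risk, within-study scan spread and whether births before 24 weeks count as events, none of which the SAP gives.

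It would be wrong to conclude that the primary CL association is materially biased. Attenuation was about 0–2.5% on the log scale, with one extreme scenario near 3.7%, and appreciable only if CL falls with scan week, a relationship SAP 4.3 plans only to describe. The change is worth making because the early curves matter for absolute risk and the remedy is cheap.

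**What to change.** State in SAP 2.4.1, for both outcomes and for the cumulative incidence curves, that the time scale is gestational age with delayed entry at the selected scan: `Surv(GA_measurement, GA_delivery, event)`, censored at 37 weeks.

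For studies with only a study-level scan range, use the mean already imputed under SAP 2.4.2 as the entry time. Add a rule for women who deliver before that imputed week, since their entry would fall after their exit; for example, leave them out of the fit and report how many there are per study. Add one sensitivity analysis that either starts risk at 24 weeks (landmark) or omits these studies from the early part of the curves. Entering such studies at the upper limit of their range should not be the default: it discards every birth before that limit and conflicts with the imputed mean.

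Cost: a sentence or two in the SAP and one model argument, using listed variables. There are two downsides. A few early events in range-only studies need the handling rule. Risk sets just after the earliest scans will also be small, most of all in the smaller studies (Table 2 runs from 103 to 1,229 women), so each curve should begin at a stated week with enough women under observation.
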